#### Mediation measures

To further understand how the interventions’ components may affect behaviour change, participants will be asked to report on psychosocial factors believed to be important markers of behaviour change.^53 54 62–64^ Confidence, importance and know-how will be measured using single face-valid items (see online supplemental appendix B), a limitation which we point out in the discussion but which we find necessary in order to reduce participant burden. These measures will be used to estimate to which degree the total effects of the components of the intervention are mediated through these factors.

### Participant timeline and follow-ups

A trial participant timeline is presented in figure 1. Intervention components (depending on allocation) will be made available to participants all at once and stay available to participants at their own discretion throughout the 4-month trial period. There are three follow-up stages: 1, 2 and 4 months after randomisation. All follow-ups will be initiated by sending text messages to participants with hyperlinks to questionnaires. The following additional attempts will be made to collect data:

A total of two text reminders will be sent 2 days apart to those who have not responded.If there is no response to the mediator questions at the 1-month follow-up, then the questions will be sent in a text message and participants are asked to respond directly with a text.If there is no response to the 2-month and 4-month follow-ups, then we will call participants to collect responses for the primary outcome measures only. A maximum of five call attempts will be made.

**Figure 1 F1:**
[figure not shown]
SPIRIT figure depicting participant timeline. SPIRIT, Standard Protocol Items: Recommendations for Interventional Trial.

### Assignment of interventions

Randomisation will be fully computerised, and allocation will be done automatically. Block randomisation will be used to allocate participants equally among the 64 factor conditions with random block sizes of 64 and 128. Neither research personnel nor participants will be able to influence the allocation.

Research personnel will be blind to allocation throughout the trial, although there is risk for potential disclosure during follow-up through phone calls (see the Limitations). The factorial design will allow all participants to have access to the intervention (although different components), and they will not be made aware of the other available conditions and will therefore be blind to allocation.

### Patient and participant involvement statement

During the process of designing the intervention content, 24 students at Linköping university were individually interviewed about their views on lifestyle in general, behaviour change, and the use of digital technology to support change. These interviews informed the content of the intervention, as did our previous research findings from formative development processes and user evaluation of digital interventions among Swedish university students.^29 65–67^ Our previous research also informed decisions about burden of the intervention and time required to participate.

Participants in the trial will after the 4-month follow-up be asked if they wish to participate in a post-trial interview. The purpose of the interviews is to explore strategies used by participants to change their behaviour. We will randomly select participants each week among those who report interest, stratifying for age, gender, baseline risk factors and allocation to ensure that we cover a heterogeneous group with respect to these variables, with a target of 20–30 interviews.

Outcome measures used in the trial are informed by national guidelines in Sweden, as well as those set by the WHO. Also, the Swedish National Board of Health and Welfare^59^ have reported that research regarding multiple lifestyle behaviour change interventions is lacking.

## Analysis

Analyses will be done under the intention-to-treat principle including all randomised participants. Analyses will be done using available data and imputation. Imputation will be done using multiple imputations with chained equations.^68^ The implicit missing at random (MAR) assumption underlying this approach will be investigated by two attrition analyses: (1) if data is missing systematically then it may be the case that early responders (ie, those who answer without reminders) differ from non-responders, and in extension that late responders (ie, those who require several attempts) are more alike non-responders. Therefore, one attrition analysis will regress primary outcomes against number of attempts to collect follow-up before a response was recorded; (2) we will further explore the MAR assumption by investigating if responders and non-responders are different with respect to baseline characteristics.

Longitudinal data will be analysed using multilevel models with adaptive intercepts for participants and time by component interactions. Bayesian inference will be used to estimate the parameters of the models^30 31 69^ (see Sample Size for priors). For each condition by time coefficient, we will report the marginal posterior probability of effect, and the median will be used as a point estimate of the magnitude of the effect. We will also report on 50% and 95% compatibility intervals.

### Models

#### Objective 1: primary and secondary outcomes

Analyses of primary outcomes will be conducted among those fulfilling the respective criteria for inclusion at baseline, for example, weekly alcohol consumption will be analysed among those who reported having consumed 10/15 (female/male) or more units of alcohol the past week. BMI, candy/snacks and stress will be analysed among all participants, and number of cigarettes smoked weekly among baseline smokers.

Weekly alcohol consumption, frequency of heavy episodic drinking per month, weekly intake of candy and snacks, number of sugary drinks per week, and cigarettes smoked per week are all count variables that are likely skewed and over dispersed. Therefore, these outcomes will be analysed using negative binomial regression. If found not to be over dispersed, we will consider using normal regression (possibly log-transformed). Average intake of fruit and vegetables per day, MVPA minutes per week, BMI, and stress will be analysed using normal regression (possibly log-transformed). Point prevalence of smoking abstinence will be analysed using logistic regression.

All models will be adjusted for age, gender and mediators at baseline. We will investigate pairwise interactions among components. Effect modification will be explored in all models to assess if any of the baseline characteristics moderate the effects of the components of the intervention.

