### Sample size, effect, harm and futility

The trial will use a Bayesian group sequential design^48–50^ to monitor recruitment with interim analyses planned for every 50 participants completing the 4-month follow-up. Each of the primary outcomes will be modelled according to the analysis plan (see Analysis), and coefficients for dummy variables representing presence/absence of each component will be assessed for effect, harm and futility with respect to each outcome. We let ß_k, l, i_ represent the regression coefficient for component *k*, at time l, for outcome *i*, and D all the data currently accumulated, then the target criteria will be:

**Effect (fruit/vegetable and physical activity):** p(ß_k, l, i_ > 0 | D)>97.5% and p(ß_k, l, i_ > 0.10 | D)>50%.
**Harm (fruit/vegetable and physical activity):** p(ß_k, l, i_ < 0 | D)>97.5% and p(ß_k, l, i_ < -0.10 | D)>50%.
**Effect (sugary drinks, alcohol and smoking):** p(ß_k, l, i_ < 0 | D)>97.5% and p(ß_k, l, i_ < -0.10 | D)>50%.
**Harm (sugary drinks, alcohol and smoking):** p(ß_k, l, i_ > 0 | D)>97.5% and p(ß_k, l, i_ > 0.10 | D)>50%.
**Futility (all outcomes):** p(−0.10 < ß_k, l, i_ < 0.10 | D)>95%.

Outcomes analysed using normal regression will be standardised when checking the above criteria. For the effect and harm criteria, we will use a standard normal prior for dummy covariates (mean=0, SD=1.0), and a slightly wider prior will be used for the futility criterion (mean=0, SD=2.0). The criteria should be viewed as targets, thus, at each interim analysis, we will evaluate each criterion and make a decision if we believe that recruitment should stop or continue. We will consider removing factors from the trial if the harm criteria are fulfilled. Note that we are estimating each component’s effect on each outcome, thus we are not a priori excluding any combination. If a component is ineffective with respect to a specific outcome, then this will be captured by the futility criteria, and will also be reported as a finding.

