While the final sample size is not determined a priori, we conducted a series of simulations with effect sizes at the minimal value of the above criteria (0.1 Cohen’s d for fruit/vegetable and physical activity, 1.1 incidence rate ratios for sugary drinks and alcohol and 1.1 ORs for smoking). Simulations suggested that approximately 1500–2500 participants will be necessary to recruit. However, the criteria will decide, not the simulations. Recruitment will last no longer than 24 months despite criteria being fulfilled or not. Despite having more conditions than in a traditional two-arm trial (in this case, 64 conditions), the factorial design is fully powered for each contrast.^47^ This can be understood by observing that half the study population are given access to each individual component (see Table 1 in online supplemental appendix 3), thus the other half creates a contrast (a type of control).

Note that the Bayesian approach allows us to make unlimited looks at the data without worrying about multiplicities and error rates, as would be necessary using a frequentist approach.^73^ Also, since no fixed effect size is prespecified, we reduce the risk of stopping recruitment both too early and too late.^50^

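### For the three primary count outcomes, the optional fallback to normal regression would turn the 0.10 decision threshold from a log rate ratio into 0.10 SD

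*Protocol article*

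**What the plan says.** Three statements in the protocol article bear on this.

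- **Models, Objective 1.** The count outcomes "are all count variables that are likely skewed and over dispersed". The text continues: "Therefore, these outcomes will be analysed using negative binomial regression". It then adds a fallback: "If found not to be over dispersed, we will consider using normal regression (possibly log-transformed".
- **Sample size, effect, harm and futility (criteria).** Each primary outcome is modelled at the interim looks as in the analysis section. For sugary drinks and alcohol, the magnitude part of the effect rule is "p(ß_k, l, i_ < -0.10 | D)>50" per cent, alongside a 97.5% probability that the coefficient is below zero. Futility needs 95% probability that the coefficient lies within ±0.10, for every outcome. The section adds: "Outcomes analysed using normal regression will be standardised when checking the above criteria".
- **Same section (simulations).** The minimal effects were "0.1 Cohen’s d for fruit/vegetable and physical activity" and "1.1 incidence rate ratios for sugary drinks and alcohol".

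Three of the six primary outcomes are counts: weekly alcohol, heavy episodic drinking and sugary drinks. Cigarettes and candy/snacks are also counts but are secondary, so the stopping criteria do not apply to them.

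**The concern.** The limit of 0.10 is a bare number whose meaning comes from the model. Under a log-link count model it is a log rate ratio, which is how the simulations treat alcohol and sugary drinks. Under normal regression with standardisation it is a tenth of a standard deviation, a meaning the simulations give only to fruit/vegetables and physical activity. If the fallback were used for a count outcome, the hurdle for effect, harm and futility would change with a data-driven choice of model and would no longer be on the simulated scale. The article does not re-express the threshold for that case.

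The stated trigger is also a weak reason to leave count regression. Negative binomial regression has Poisson regression as its limit, so a lack of over-dispersion can be handled on the same log-rate scale.

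**Working it through.** **Plan's own figure.** exp(0.10) = 1.105 and ln(1.1) = 0.0953, so 0.10 on the log scale agrees with the stated rate ratio of 1.1. A coefficient of −0.10 is a reduction of 1 − exp(−0.10) = 9.5%. The range of 1500–2500 participants cannot be reproduced, because the simulation inputs are not in the article.

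**Inputs that must be assumed.** Follow-up means and variances are not given. Means of 1, 3, 10 and 15 are used because they are the entry cut-offs: one heavy episode a month, three sugary drinks a week, and 10/15 alcohol drinks a week for women/men.

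**What 0.10 SD means.** As a fraction of the mean it is 0.10 × SD/mean. With variance equal to the mean this is 0.10/√mean. The models include participant intercepts, so dispersion might instead be judged given those intercepts. With between-person SD s on the log scale, the expression becomes 0.10 × √(1/mean + exp(s²) − 1).

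| Mean | s = 0 (variance = mean) | s = 0.5 | s = 0.75 | s = 1 |
|---|---|---|---|---|
| 1 | 10.0% | 11.3% | 13.2% | 16.5% |
| 3 | 5.8% | 7.9% | 10.4% | 14.3% |
| 10 | 3.2% | 6.2% | 9.2% | 13.5% |
| 15 | 2.6% | 5.9% | 9.1% | 13.4% |

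The comparator throughout is 9.5%. With s = 0 the two scales agree at a mean of (0.10/0.0952)² = 1.10. With s around 0.75 the gap is nearly closed at means of 3 to 15, and beyond that it reverses.

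**Log-transformed variant.** For equidispersed counts, using positive values only, 0.10 SD of the log is a 3.4% change at mean 10, 5.5% at mean 3 and 4.3% at mean 1. A log model would keep the 9.5% meaning only if it were not standardised, but the criteria section says that normally modelled outcomes are.

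**Futility.** Take one time point, half the participants at each level, a near-flat prior and variance equal to the mean. The standard error is about 2/√(n × mean) on the log-rate scale and 2/√n on the SD scale. For an estimate of zero, futility needs 1.96 × SE ≤ 0.10.

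- Log-rate scale: n ≈ (1.96 × 2/0.10)²/mean = 1537/mean, about 154 at mean 10 and 512 at mean 3.
- SD scale: n ≈ 1537 whatever the mean.

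**Effect rule, both clauses together.** Take n = 500 in one outcome's analysis set, as an illustration. On the SD scale the 97.5% clause needs 1.96 × 2/√500 = 0.175 SD, which already exceeds 0.10 SD. Dividing by √mean gives the reduction needed.

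- Mean 10: 5.5%, against 9.5% on the rate-ratio scale, about 42% lower.
- Mean 5: 7.8%, against 9.5%, about 18% lower.
- Mean 3: 10.1%. On the log-rate scale the 97.5% clause needs 1.96 × 2/√1500 = 0.101, so it binds there too and the bar hardly moves.

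**The case against.** The strongest reply is that this may never arise. The article expects over-dispersion, makes negative binomial regression the stated model, says only that normal regression would be considered, and calls the criteria targets to be weighed at each look. That stands, and it makes this a contingency. It does not reconcile the three statements if the fallback is used.

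A reader might infer that the effect bar would fall from 9.5% to 3–6% in general. The documents do not support that. The percentages rest on means and variances that are not given, they reach 10% at a mean of 1, and between-person variation narrows or removes the gap at higher means. The effect rule also has the 97.5% clause, which binds first on the SD scale until about 1537 participants are in that outcome's analysis set. Each set is limited to those meeting their own entry criterion. If the 25% risky-drinking figure from the Introduction applied to 1500–2500 recruits, the alcohol set would hold 375–625, though the recruited share may be higher.

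A reader might also infer that the model will be re-selected from look to look. No statement says so; the text is only silent on whether the model is fixed. Finally, log(0) is undefined, but handling zeros, for example with an added constant, can be left to the analysis plan and is not part of this point.

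The article does give 0.1 a separate meaning for each outcome (Cohen's d, rate ratio, odds ratio). That tie is by outcome, and the fallback is what would break it.

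**Conclusion.** The inconsistency is real but conditional. If a primary count outcome moved to normal regression, the unchanged ±0.10 limits would cease to be the log rate ratio on which the simulations rest. With variance equal to the mean, the limit would go from 9.5% to about 3% at a mean of 10 and 6% at a mean of 3, with almost no change (10%) at a mean of 1. These means are assumptions.

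The clearest consequence is for futility: where 0.10 SD is the smaller quantity, the band narrows and futility becomes harder to declare. At a mean of 10 the number needed for an estimate of zero would rise from about 154 to 1537. The magnitude clause for effect and harm loosens by the same factor, but the full effect rule loosens only where the 97.5% clause is not already the stricter one. The point is worth correcting because the remedy is small, not because the switch is likely.

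**What to change.** Either of two changes resolves it.

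1. Replace the fallback with count regression throughout: negative binomial, or Poisson if dispersion is negligible, for all count outcomes at every look and at the final analysis.
2. Keep the fallback, but state that for count outcomes the 0.10 thresholds are evaluated on the rate-ratio scale whichever model is used, and that the model is fixed across looks.

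The first is simpler and keeps the stopping rules on the simulated scale. Either is an edit of a sentence or so. The small downside of the first is that if counts proved under-dispersed, negative binomial and Poisson models would slightly overstate the variance.

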#### Objective 2: mediator outcomes

Mediators will be explored using a causal inference framework,^70–72^ using Bayesian inference to estimate the natural direct effect and natural indirect effect (as per the definitions of Pearl^72^). We will report on the posterior distributions of these two estimates, as well as the proportion of the total effect which is accounted for by the natural indirect effect. Four models will be created for each primary outcome measure, three which investigate the mediating factors on their own, and a fourth which incorporates all mediators at once. If any baseline characteristics were found to moderate the effect in the primary analysis, then additional mediator models will be created to include these as moderators.

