**Methods and analysis:**

A factorial randomised trial (six factors with two levels each) will be employed to estimate the effects of the components of a novel mHealth multiple lifestyle intervention on alcohol consumption, diet, physical activity and smoking among Swedish college and university students. A Bayesian group sequential design will be employed to periodically make decisions to continue or stop recruitment, with simulations suggesting that between 1500 and 2500 participants will be required. Multilevel regression models will be used to analyse behavioural outcomes collected at 2 and 4 months postrandomisation.

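### Objective 2 plans natural direct and indirect effects, but early behaviour change that alters the 1-month mediator scores would confound them, and the models make no allowance for it

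*Protocol article*

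**What the plan says.** All places are in the protocol article.

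- **Exposure** (Participant timeline and follow-ups). Allocated components "will be made available to participants all at once and stay available to participants at their own discretion throughout the 4-month trial period".
- **Contacts** (same section). "There are three follow-up stages: 1, 2 and 4 months after randomisation".
- **Mediators** (same section). The fallback by text message begins "If there is no response to the mediator questions at the 1-month follow-up", which places the post-randomisation mediator questions at 1 month.
- **Behaviour** (Abstract, Methods and analysis). The regression models are for "behavioural outcomes collected at 2 and 4 months postrandomisation". The telephone back-up covers the same two times: "If there is no response to the 2-month and 4-month follow-ups, then we will call participants to collect responses for the primary outcome measures only".
- **Estimand** (Objective 2: mediator outcomes). The analysis works within a causal framework, "using Bayesian inference to estimate the natural direct effect and natural indirect effect". It also reports the share of the total effect that is indirect. Each primary outcome gets four models: one per mediator and one with all three.
- **Adjustment** (Objective 1: primary and secondary outcomes). All models adjust for age, gender and baseline mediators. Objective 2 adds only baseline characteristics found to be moderators. Nothing measured after randomisation enters except the mediators themselves.
- **Stated caveat** (Limitations). The caution about mediation concerns whether single items capture importance, confidence and know-how in full.

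**The concern.** A natural indirect effect needs, among other conditions, that no common cause of mediator and outcome is itself affected by the exposure. Here the mediator is scored after about a month of full access to the components. Someone who has already cut down or become more active may rate confidence, know-how or the importance of further change differently because of it. Month-1 behaviour also predicts behaviour at 2 and 4 months. If the component moved it, the condition fails.

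Randomisation does not help, because the mediator is not randomised. Adjustment for baseline variables does not remove the problem, because the confounder arises after baseline.

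At stake is the reading of Objective 2, which the Aims section lists as a study objective. A score that merely reflects change already made could be credited with producing it, and components might be redesigned around importance, confidence or know-how on that evidence.

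**Working it through.** The protocol gives no figure for the mediation analysis, so there is none to reproduce. The check asks what the planned type of model returns when the mediator truly has no effect on the outcome.

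**From the protocol.** Timing, estimand and baseline-mediator adjustment as above; N = 2000, inside the expected 1500 to 2500.

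**Assumed (the protocol gives no values).** X is the component (0/1), B0 and B1 behaviour at baseline and month 1, M0 and M1 the mediator score at the same times, Y the later outcome, and e independent standard normal errors.

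- M0 = 0.3·B0 + √0.91·e, with B0 standard normal
- B1 = a·X + 0.5·B0 + √0.75·e
- M1 = m·X + 0.4·M0 + c·B1 + 0.8·e
- Y = r·B1 + 0.1·B0 + 0.75·e

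M1 does not appear in Y, so the true indirect effect is 0.

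**Formulas, adjusting for M0.**

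- Variance of B1 given X and M0: 0.25 × 0.91 + 0.75 = 0.9775
- Covariance of B1 and B0 given X and M0: 0.5 × 0.91 = 0.455
- False mediator slope: b = c(0.9775r + 0.1 × 0.455) / (0.9775c² + 0.64)
- Component-to-score path: m + c·a
- Total effect: r·a
- False share: (m + c·a)·b / (r·a)

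With m = 0 the share is c·b/r. Because b has the sign of c, the share is positive whether early change raises or lowers the score.

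**Worked case, c = 0.4, r = 0.6, m = 0.** b = 0.4 × (0.5865 + 0.0455) / (0.1564 + 0.64) = 0.2528 / 0.7964 = 0.317. Share = 0.4 × 0.317 / 0.6 = 21%.

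**Results.** The simulation used 400 runs per cell. The last column is the fraction of runs in which the approximate posterior probability of a positive indirect effect passed 97.5%.

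| a | c | r | m | Share, formula | Share, simulated | Passed 97.5% |
|---|---|---|---|---|---|---|
| 0.1 | 0.2 | 0.6 | 0 | 6% | 6% | 9% |
| 0.2 | 0.2 | 0.6 | 0 | 6% | 6.5% | 21% |
| 0.3 | 0.3 | 0.6 | 0 | 13% | 13% | 63% |
| 0.2 | 0.3 | 0.4 | 0 | 13% | 14% | 36% |
| 0.2 | 0.4 | 0.6 | 0 | 21% | 20% | 49% |
| 0.2 | 0.3 | 0.6 | 0.2 | 56% | 55% | 100% |

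The last row lets the component also move the inert score directly.

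**Adding baseline behaviour.** The slope becomes b = 0.75·c·r / (0.75c² + 0.64). At c = 0.4, r = 0.6 this is 0.18 / 0.76 = 0.237, and the share is 0.4 × 0.237 / 0.6 = 16%. Across the five rows with m = 0 the simulated share was 5% to 16%, so roughly three quarters of the false share remains. In the last row it was 41%.

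**Controls.** With c = 0 (behaviour does not alter the score) the false indirect effect was 0. With a = 0 and m = 0 it averaged 0. With B1 added to the outcome model, the false slope and indirect effect were 0 in every scenario.

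**The case against.** Several points on the other side stand.

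- **The 1-month questionnaire is not shown.** It is in appendix B, and the timeline figure is missing too. A reader might infer that behaviour is certainly not asked at 1 month, or that mediators are never asked again. The text is consistent with the first but states neither. What it does show is that the described models contain no month-1 behaviour.
- **Early change is not documented.** Use is at the participant's discretion over 4 months, and nothing says how much behaviour moves in the first. The point is therefore conditional.
- **A larger size is tempting.** In a bare linear model without covariates, where the whole effect runs through month-1 behaviour, the false share equals the squared correlation of score and behaviour: 9% at 0.3 and 36% at 0.6. That leaves out the planned baseline-mediator adjustment and should not be carried over. The linear working is also not shown to hold for the four primary outcomes planned as negative binomial or logistic.
- **Detection is not assured.** Take a false component-to-score path of 0.03 to 0.06 at N = 2000, with standard error about 2/√2000 = 0.045 for a unit-SD score. The 97.5% threshold is then passed in only about 10% to 27% of trials. Primary outcomes are analysed in those meeting the respective criterion, so those samples are smaller still. The estimate is biased either way.
- **A condensed article may leave sensitivity analyses to the analysis plan.** True, and their absence alone would be no finding. But the article itself fixes the measurement times and the natural-effect estimand, and those create the problem.

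Two points carry less weight. The protocol says mediators will be explored, yet the Aims list the degree of mediation as an objective, and only Objective 3 is expressly labelled exploratory. The mediator does precede the outcome measurement, but not necessarily the behaviour change.

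**Conclusion.** The concern holds in conditional form. If components change behaviour in the first month and that change alters the scores, the planned natural effects are not identified in general, and an inert mediator can appear to carry part of the effect. Under the assumed linear parameters, with baseline mediators adjusted, the false share is about 6% to 20%. It reached 55% in the scenario where the component also moved the score directly. The true size is unknown.

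The documents do not support the stronger conclusion that a spurious indirect effect will be reported: that needs early change, an effect of it on the scores, and enough precision to show it. Only the mediation conclusions are affected; the primary component effects and the stopping criteria are not. The change is worth making because it is cheap and alters what Objective 2 can claim.

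**What to change.** 1. **Sensitivity analysis.** For each natural indirect effect, add an analysis for unmeasured mediator-outcome confounding on a scale that fits the model. For the normal models, use the residual correlation of mediator and outcome. For the negative binomial and logistic models, where that correlation is not directly defined, use an unmeasured-confounder or latent-variable parameter on the link scale. Report the confounding strength at which the 95% interval first includes zero. Set no fixed pass mark such as 0.5; no agreed threshold exists.
2. **Wording.** State in Objective 2 that the decomposition and the proportion mediated are causal only if early behaviour change does not drive the scores, and otherwise describe them as associations.

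The cost is extra model runs and a weaker causal claim. The sensitivity analysis bounds the bias; it does not remove it.

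Asking the behaviour questions at 1 month, if they are not already asked, is optional. It would allow interventional rather than natural indirect effects that account for month-1 behaviour, but it adds to the participant burden the authors chose to limit. The recommendation does not depend on it.
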